## **4. Method**

### **(1) Allocation**

A hundred and eighty eligible patients will be randomly assigned to the LMA group (Group L) and ETT group (Group E) at a 1:1 ratio.

### **(2) Anesthesia management**

Routine monitoring will be performed after participants enter the operating room, including electrocardiogram, non-invasive blood pressure (BP), pulse oxygen saturation ( $\text{SpO}_2$ ), bispectral index, and temperature. Intravenously administered  $0.025\text{--}0.075 \text{ mg} \cdot \text{kg}^{-1}$  midazolam as a premedication.  $0.3\text{--}0.5 \text{ } \mu\text{g} \cdot \text{kg}^{-1}$  sufentanil,  $1.5\text{--}2.5 \text{ mg} \cdot \text{kg}^{-1}$  propofol, and  $0.15 \text{ mg} \cdot \text{kg}^{-1}$  cisatracurium will be administered for anesthesia induction. After 3 min of pre-oxygenation, the anesthesiologist in charge will establish an artificial airway according to the allocation information and cover an asepsis scarf to ensure that the intervention is blinded to the lung ultrasound assessor. Anesthesia maintenance will be administered with a total intravenous infusion of  $6\text{--}8 \text{ mg} \cdot \text{kg}^{-1} \cdot \text{h}^{-1}$  propofol and  $0.2\text{--}0.3 \text{ } \mu\text{g} \cdot \text{kg}^{-1} \cdot \text{min}^{-1}$  remifentanyl according to patients' circulation conditions and anesthesia depth. Mean arterial pressure (MAP) and heart

rate (HR) will remain within 30% of the baseline level, and the temperature will remain within 36–37°C during operation. If necessary, vasoactive agents will be used to maintain stable circulation, and the agent type, dosage, and use time will be recorded accurately. Lung protective ventilation strategy will be applied during operation and related parameters are set as follows: tidal volume ( $V_t$ ) at 6–8 mL·kg, PEEP=5 cmH2O, with recruitment maneuver (in total of three times, each time with a pressure of 30 cmH2O for 10 s), I:E=1:1.5, FiO2 at 0.4, oxygen flow rate at 1.5 L/min, and respiratory rate (RR) at 12–20 bpm to maintain the end-tidal carbon dioxide partial pressure ( $P_{ET}CO_2$ ) range from 35 mmHg to 45 mmHg. All anesthetic infusions will be discontinued at the end of surgery. The postoperative transfer location, including the postoperative anesthesia care unit or intensive care unit, will be decided together by the anesthesiologist and surgeon. Flurbiprofen axetil intravenously or acetaminophen orally are administered for necessary postoperative analgesia, and the dose and time of administration will be accurately recorded.

### (3) Lung ultrasound

Lung ultrasound assessment will be performed by a blinded trained anesthesiologist. As shown in a previous study, ultrasound scanning will select a 5–12 MHz linear transducer (SonoSite M-Turbo) to parallelly scan all the intercostal space of 12 regions from right to left, anterior to posterior of patients' chest in the supine position. The six regions are divided by anterior midline, clavicular midline, anterior axillary line, posterior axillary line, and pectoral nipple line in each hemithorax. This anesthesiologist will complete the assessment according to the LUS criteria at the same time as scanning, and the significant images and videos will be recorded.

Atelectasis LUS criteria: 0 indicates normally ventilated areas with lung sliding sign: A-line, or isolated B-lines (< 3); 1 indicates a mild reduction in lung ventilation/moderate loss of lung tissue gasification; B lines ( $\geq 3$ ) with clear boundary, regular distribution, and spacing  $\geq 7$  mm, or irregular, clear interval; 2 indicates a severe reduction in lung ventilation/severe lung tissue gasification: multiple coalescent B-lines spaced  $\leq 3$  mm and continuous fusion; 3 indicates atelectasis/pulmonary consolidation: tissue-like signs, fragment signs, and bronchial inflation signs.

[figure not shown]

### (4) Intervention

Group L: In this group, LMA are selected for the artificial airway to maintain mechanical ventilation during general anesthesia. LMA size depends on the weight of the patients. After anesthesia induction and 3 min pre-oxygenation, the LMA will be inserted at the appropriate position and fixed properly.

Group E: In this group, ETT are selected for the artificial airway to maintain mechanical ventilation during general anesthesia. Normally, men and women choose a tube with the inner diameter (ID) = 8 mm, and 7.5 mm, respectively. Similar to Group L, ETT will be intubated with appropriate depth and fixed properly in the trachea after anesthesia induction.

## 5. Outcomes

Three time points were significant for outcome measurement, including 15 min after the establishment of the artificial airway ( $T_1$ ), the end of surgery ( $T_2$ ), and 30 min after extubation ( $T_3$ ). In addition, when patients enter the operation room ( $T_0$ ), they will accept the lung ultrasound assessment for the basic LUS.

**Primary outcome:** Total atelectasis LUS of 12 lung regions at  $T_1$ .

### Secondary outcomes:

- 1) Total atelectasis LUS of 12 lung regions at  $T_2$ ,  $T_3$ ;
- 2) Oxygenation index ( $\text{PaO}_2/\text{FiO}_2$ ) at  $T_1$ ,  $T_2$ ,  $T_3$ ;
- 3) Incidence of postoperative airway complications such as hoarseness, dysphagia, and sore throat during 24 h and 48 h after surgery
- 4) The incidence of PPCs[26] during 24 h and 48 h after surgery;
- 5) Length of stay.

## 6. Data collection and follow-up

The indicators that were recorded included baseline data, perioperative data, and follow-up data. All records can be found in the case report form (CRF).

Baseline data included: 1) Participants' general information such as age, height, weight, and vital signs such as basic HR, MAP, RR, and  $\text{SpO}_2$ ; 2) ASA physical status; 3) Mallampati status; 4) preoperative complications; and 5) preoperative laboratory parameters.

Perioperative data included: 1) Vital signs (HR, MAP, RR, and  $\text{SpO}_2$ ) will be recorded every 15 min from the beginning of the operation to 30 min after extubation; 2) Mechanical ventilation parameters ( $V_t$ , plateau pressure [ $P_{\text{plat}}$ ], airway peak pressure [ $P_{\text{peak}}$ ], and dynamic lung compliance [ $C_{\text{dyn}}$ ] [ $C_{\text{dyn}} = \text{tidal volume}/\{\text{PIP}-\text{PEEP}\}$ ]) will be recorded every 15 min from the beginning of the operation to extubation; 3) Atelectasis LUS at  $T_0$ ,  $T_1$ ,  $T_2$ , and  $T_3$ ; 4) Arterial blood-gas analysis results at  $T_0$ ,  $T_1$ ,  $T_2$ , and  $T_3$ ; 4) Administration of perioperative medicines, complete with the type, dosage, way, and time; 5) Several important durations, including the duration of anesthesia, operation, mechanical ventilation duration, and

extubation; and 6) Intraoperative quantity of liquid intake, urine, and blood loss.

Follow-up will be performed by the blinded and trained researchers at 24 h and 48 h. Postoperative complications, length of stay, and adverse events during hospitalization will be recorded in detail in the CRF.

## **7. Harm and solution**

If adverse events or serious adverse events (such as reflux aspiration, serious leakage of LMA, severe circulatory instability) occur intraoperatively or postoperatively,

PI and the Institutional Review Board (IRB) will be informed immediately. The IRB and PI have the right to break the blinding, if necessary.

## **8. Data preservation and confidentiality**

Participants will be asked whether relevant data can be used when signing informed consent. Each patient will be assigned a unique study identifier after they are recruited in the study to conceal and protect private information. This trial does not involve the collection of biological specimens for storage. All paper materials will be stored in the locked cabinet of the anesthesiology department of Beijing Tiantan Hospital. The electronic data will be stored in the database. Only PI has access to all information. If the researchers in charge of the result analysis need access, they need to apply access permission from PI, and access time will be recorded in detail.

## **9. Data motoring**

The data management committee consists of PI, and two statisticians will provide monitoring, including verifying the progress of the study and all observational data. Quality control was performed at all stages of the data processing. There is no interim analysis plan for our study because of the low-risk intervention and short-term research periods.

## **10. statistical analysis**

Statistical analysis will be performed using SPSS software (version 23.0; International Business Machines Inc., USA). Continuous variables will be presented as mean  $\pm$  standard deviation ( $\bar{x} \pm s$ ) media, or interquartile range, and categorical variables will be presented as numbers (proportion, %). Kolmogorov–Smirnov tests will be performed to detect the normal distribution of continuous variables. After testing for normality of continuous variables, the Student's t-test, analysis of variance, or the Mann-Whitney U-test will be used for appropriate comparisons between and within groups. Chi-squared and Fisher's exact tests will be used to analyze categorical variables. All tests will be two-tailed and conducted at a 5% significance level. Statistical significance will be set at  $P < 0.05$ . The participants missing the primary outcome will be excluded from the outcome analysis, and multiple imputations will be conducted if the unintended drop-out rates are more than 10%.

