### **(2) Sample size calculation**

Our pre-tests estimated that the atelectasis LUS in ETT was  $8.2 \pm 3.87$ . The difference in LUS, at least for a score of 2, is considered clinically significant. The alpha level was set at 0.05, the beta value was set to 0.1, and allowing for a dropout

rate of 10%. We calculated that the total sample size required 180 patients (90 patients in each group).

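### A normality test on the observed data chooses the primary test for the T1 lung ultrasound score, so the effect measure is not fixed in advance

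*Protocol*

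**What the plan says.** Protocol section 10 states one rule for all continuous variables. Kolmogorov–Smirnov "tests will be performed to detect the normal distribution of continuous variables". Then: "After testing for normality of continuous variables, the Student's t-test, analysis of variance, or the Mann-Whitney U-test will be used", as appropriate for comparisons between and within groups. Summaries follow the same logic, with mean and SD or median and interquartile range. No test or effect measure is named for the primary outcome, and "All tests will be two-tailed and conducted at a 5% significance level".

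Section 5 defines the primary outcome as "Total atelectasis LUS of 12 lung regions at" T1, which is 15 minutes after the airway is established. Section 4(3) scores each region 0, 1, 2 or 3; at the top of the scale, "3 indicates atelectasis/pulmonary consolidation: tissue-like signs, fragment signs, and bronchial inflation signs".

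Section 3(2) sizes the trial on a pre-test LUS of 8.2 ± 3.87 in the endotracheal tube group. It adds: "The difference in LUS, at least for a score of 2, is considered clinically significant". And: "The alpha level was set at 0.05, the beta value was set to 0.1".

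**The concern.** Twelve integer scores of 0 to 3 add up to an integer from 0 to 36 with many ties. Such a score cannot be exactly normal, so a normality test responds in part to its discreteness. Discreteness has little bearing on whether a comparison of means is sound with 80 to 90 patients per arm.

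The two branches also answer different questions. The t-test compares means and yields a difference in LUS points, which is what the trial was sized on. The Mann-Whitney test compares ranks. If the pre-test sends the analysis there, the plan gives no estimate or interval to set beside the 2-point threshold.

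The rule is incomplete as well. It does not say whether the Kolmogorov–Smirnov test is corrected for estimating the mean and SD from the same data, whether it is run per arm or pooled, or what follows if one arm passes and the other fails. Each of these can decide the primary test after the data are seen.

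**Working it through.** **1. The plan's own figure.** Inputs from sections 3(2) and 10: difference 2, SD 3.87, two-sided alpha 0.05, power 0.90, dropout 10%. For a comparison of means:

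n per arm = 2 × (1.960 + 1.282)² × 3.87² / 2² = 78.7, so 79.

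Allowing for dropout, 79 / 0.9 = 87.8, so 88 per arm and 176 in total. The exact t-test gives 80 per arm, 80 / 0.9 = 88.9, so 89 per arm and 178 in total. Both agree with the stated 180 to within 3%. One-sided or 80%-power versions give 53 to 73 per arm after dropout and do not fit. The trial is therefore sized for a two-sided comparison of means.

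**2. What the pre-test does.** Simulated trials used 81 per arm (90 × 0.9) and 90 per arm, mean 8.2 against 8.2 or 6.2, and SD 3.87, with 2,500 trials per scenario. Three shapes were assumed, because the protocol gives none: a continuous normal; the same normal rounded to integers and held within 0 to 36; and a right-skewed negative binomial count. Normality counts as rejected if at least one arm fails at 5%, which is also an assumption. "Corrected" means critical values that allow for the estimated mean and SD (Lilliefors).

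| Assumed shape | Rejected, corrected | Rejected, uncorrected |
|---|---|---|
| Continuous normal | 9–10% | 0% |
| Normal, rounded to integers | 66–76% | 2% |
| Right-skewed count | 97–99% | 21–47% |

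The first two rows differ only by rounding and truncation to the scale. For the rounded normal at 81 per arm, a software library's tabulated correction gave 58–64% instead, so roughly 60–80% is a fair reading. Testing the pooled arms gave 84–91% corrected and 5–8% uncorrected.

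**3. Effect on error rates.** Over all scenarios:

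- Type I error of the two-stage procedure: 4.3–6.1% (Monte Carlo standard error about 0.4 points), tracking the single tests in the same runs.
- Power of the two-stage procedure at 2 points: 89–96%.
- t-test and Mann-Whitney on opposite sides of P = 0.05: 1.5–5% of trials.
- Significance verdict changed by using the corrected rather than the uncorrected form: 1.3–2.5% of trials (rounded normal and skewed count).

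**4. A fixed comparison of means.** Exact t-test power at 2 points is 90.5% with 81 per arm and 93.2% with 90. Adjusting for T0 LUS reduces the SD to 3.87 × √(1 − ρ²), where ρ is the T0–T1 correlation. The protocol gives no ρ. An assumed 0.3 gives an SD of 3.69 and about 93% power with 81 per arm; 0.5 gives 3.35 and about 97%.

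**The case against.** The strongest reply is that little goes wrong in practice. Type I error holds, power holds, the sample size is unaffected, and the choice between tests alters the significance verdict in only a few percent of trials. That stands, and it limits the severity.

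A second reply is that the form of the Kolmogorov–Smirnov test is a detail for a statistical analysis plan, which may exist. That is fair for the form alone. It does not cover the rule itself, because the protocol positively makes the primary test depend on the observed data.

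A third is that the primary question is fixed: outcome, time point, groups, two-sided 5% level and 2-point threshold are all stated. That is correct. Only the test and the effect measure are left to the data.

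Some stronger readings are tempting but not supported:

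- A rank analysis is not beyond comparison with 2 points. A Hodges-Lehmann estimate is in LUS points, and so are medians. The gap is that the plan names no estimate for that branch.
- The two forms of the test do not always conflict. For a continuous normal score they would differ in only about 9–10% of trials.
- The protocol names SPSS 23.0 but no procedure within it, so nothing can be concluded about which form the software would apply.
- The discreteness argument does not carry over to the oxygenation index, which is a continuous ratio.

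**Conclusion.** The point holds, with moderate severity. Section 10 lets the data choose between a mean comparison and a rank comparison for the primary outcome, while section 3(2) sizes the trial only for the first. The choice can turn on integer scoring and on an unstated form of the pre-test: for a rounded normal score, roughly 60–80% rejection against about 2–3%.

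The percentages rest on assumed score shapes and on the at-least-one-arm rule. The data-dependent rule and its mismatch with the sample size basis rest on the protocol's text alone. A reader might infer an inflated false-positive rate or an inadequate sample size; the calculations show neither. What is lost is a primary effect measure settled before the data are seen, and with it protection against analyst discretion.

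**What to change.** In section 10, remove the normality pre-test for T1 LUS and name one primary analysis: the between-group mean difference in LUS points with its 95% CI, from a linear model adjusted for T0 LUS. The T0 score is already collected (sections 5 and 6). Keep the Mann-Whitney test with a Hodges-Lehmann estimate as a sensitivity analysis.

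An unadjusted t-test with a confidence interval would also cure the defect. The adjustment is recommended because it uses data already planned and gains precision if T0 and T1 scores correlate.

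The change is to wording only, and 180 patients remain sufficient. The price is a few points of power relative to a rank test if the score is markedly skewed: about 90–91% against 94–95% in the skewed simulation, unadjusted, with 81 per arm.

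### The T0 lung ultrasound score has no stated role in the primary comparison; adjusting for it would be a free gain in precision

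*Protocol*

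**What the plan says.** Protocol section 5 defines the primary outcome as "Total atelectasis LUS of 12 lung regions at" T1, which is 15 minutes after the airway is established. It is the score itself, not a change from T0. The same section says that when patients enter the operating room "they will accept the lung ultrasound assessment for the basic LUS". Section 6 lists LUS and arterial blood gas among the data recorded at T0, T1, T2 and T3.

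For continuous variables, section 10 provides a Kolmogorov–Smirnov check of normality, after which "the Student's t-test, analysis of variance, or the Mann-Whitney U-test will be used for appropriate comparisons between and within groups". It mentions no covariate, regression model, ANCOVA or change score. Section 4(1) gives 1:1 allocation and does not mention stratification by T0 LUS.

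Section 3(2) sizes the trial on a pre-test LUS of 8.2 with SD 3.87 in the endotracheal tube arm. It adds: "The difference in LUS, at least for a score of 2, is considered clinically significant". It assumes no gain from a baseline covariate.

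**The concern.** T0 LUS is measured before the intervention, on the same scale and by the same kind of assessment as the primary outcome. If patients with higher scores at T0 also tend to have higher scores at T1, part of the spread in T1 is predictable. An unadjusted test leaves that part in the error term.

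Two things are at stake. The first is the width of the interval that will be read against the 2-point threshold. The second is chance imbalance: nothing in the stated design balances T0 LUS, so a difference between arms at T0 carries into the unadjusted estimate in proportion to the T0–T1 slope. Naming the model in advance also prevents a later choice between adjusted and unadjusted results.

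**Working it through.** **Inputs from the protocol.** SD 3.87, difference 2 points, beta 0.1, dropout 10% (section 3(2)); two-sided 5% (section 10: "All tests will be two-tailed and conducted at a 5% significance level"); 1:1 allocation (section 4(1)); 90 patients per arm, hence 90 × 0.9 = 81 evaluable.

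**Assumed.** SD 3.87 applies at T1 in both arms. The within-arm T0–T1 correlation r is not in the document and is varied from 0.1 to 0.6.

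**Step 1: the plan's own figure.** Normal approximation: n per arm = 2 × [(1.960 + 1.282) × 3.87 / 2]² = 78.7, so 79. Dividing by 0.9 gives 87.8, so 88 per arm and 176 in total. The exact noncentral t gives 80 per arm, 89 after dropout and 178 in total. The stated 180 therefore reproduces as a two-sided, unadjusted comparison of means.

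**Step 2: the unadjusted analysis at 81 per arm.** SE = 3.87 × √(2/81) = 0.608. The noncentrality is 2 / 0.608 = 3.29, which gives power 90.5% (160 df). The 95% CI half-width is 1.975 × 0.608 = 1.20 points.

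**Step 3: adjustment for T0.** The residual SD under ANCOVA is 3.87 × √(1 − r²), with 159 df. SE, power and half-width follow as in step 2.

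**Step 4: chance imbalance.** A T0 difference of 1.96 standard errors is 1.96 × SD(T0) × √(2/81). The T0–T1 slope is r × 3.87 / SD(T0). In the product SD(T0) cancels, so the shift in the unadjusted estimate is r × 1.96 × 0.608.

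| r | Residual SD | Power for 2 points | CI half-width | Shift at 1.96 SE imbalance |
|---|---|---|---|---|
| unadjusted | 3.87 | 90.5% | 1.20 | – |
| 0.1 | 3.85 | 90.7% | 1.19 | 0.12 |
| 0.3 | 3.69 | 92.9% | 1.15 | 0.36 |
| 0.5 | 3.35 | 96.5% | 1.04 | 0.60 |
| 0.6 | 3.10 | 98.3% | 0.96 | 0.72 |

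The last column is what the unadjusted estimate would absorb if r had the value in that row. At r=0.5 adjustment gives 81 patients per arm the precision of 81 / (1 − 0.25) = 108.

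**Step 5: error rate given such an imbalance.** With no true airway effect, the unadjusted test rejects with probability 1 − Φ[(1.96 − 1.96r)/√(1 − r²)] + Φ[(−1.96 − 1.96r)/√(1 − r²)]. This is about 8% at r=0.3 and 13% at r=0.5. Averaged over all randomisations it stays at 5%.

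**The case against.** The strongest reply is that nothing here is wrong. Under randomisation the unadjusted comparison is valid, its interval already allows for chance imbalance on average, and step 2 shows that the trial meets its own power target. All of that stands. A reader might infer from the missing covariate that the trial is underpowered or its type I error inflated; the protocol's figures do not support either inference.

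A second reply is that covariates belong in a statistical analysis plan, which may exist but is not shown, and that section 10 is only a general list for all continuous variables. This holds in part. The list gives T0 no role, but does not expressly forbid one. Still, the section does name its methods, and all are unadjusted as named.

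A third reply is that analysis of variance and within-group comparisons could mean a repeated-measures analysis that includes T0. That is possible, but it is not stated as the primary between-arm analysis, and tests within each arm do not adjust the difference between arms.

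The fourth reply is the most substantial: r may be small. Eligibility requires age under 60 and BMI of at most 30, and excludes reactive airway disease and recent smoking or respiratory infection, which may narrow T0 scores. Section 1 describes atelectasis as arising within minutes of pre-oxygenation, so T1 may mostly reflect what happens after T0. At r=0.1 the gain is negligible.

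Finally, a reader might infer that a T0 imbalance passes in full into the estimated airway effect. It does so only after multiplication by the slope, and an imbalance of 1.96 standard errors or more is expected in only about 5% of trials.

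**Conclusion.** The point holds as a free improvement, not as a correction of an error. The protocol collects T0 LUS in every patient and gives it no stated role in the primary comparison. The direction is certain for any appreciable T0–T1 correlation. The size is not: it runs from practically nothing at r=0.1 to a CI about 20% narrower at r=0.6 (0.96 against 1.20 points). These figures rest on SD 3.87 in both arms, 81 evaluable patients per arm, a linear T0–T1 relation and the assumed values of r. If r is near zero, adjustment costs one degree of freedom.

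**What to change.** In section 10, state the primary analysis as a linear model (ANCOVA) of T1 LUS on arm and T0 LUS. Report the adjusted mean difference with its 95% CI against the 2-point threshold. Keep the unadjusted t-test or Mann–Whitney comparison as a sensitivity analysis, which also preserves the provision for non-normal data.

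Analyse T2 and T3 LUS in the same way, with T0 LUS as covariate. For PaO2/FiO2, adjust for the T0 value only if FiO2 at T0 is recorded with the T0 blood gas: section 6 schedules the gas at T0, but section 5 lists the index only from T1 on, and no T0 FiO2 is given.

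A change score is not an equivalent substitute. With equal SDs at T0 and T1 its SD is 3.87 × √(2 − 2r), which exceeds 3.87 whenever r is below 0.5.

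The cost is a few sentences, settled before outcomes are compared by arm. The LUS analyses need no new measurements or patients, and SPSS, the named software, fits the model.
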